##### Adherence

2.8.2.16.

According to the suggested guidelines regarding adherence in randomised controlled trials investigating online interventions (124), adherence to the intervention is operationalized by the percentage of completed intervention units. All assessed variables, the according measurement instruments and measurement points are depicted in Table 2. Reasons for potential dropout reasons are assessed *via* the Dropout Reasons Questionnaire for Internet Interventions (125).

**Table 2 T2:** Assessed variables, measurement instruments and measurement points.

Variables	Measurement instrument	Measurement point				
		T0	T1	T1–T2	T2	T3
Primary outcome						
Acute perceived stress	Perceived Stress Scale (PSS-10)	X				
Acute perceived stress	Perceived Stress Scale - short form (PSS-4); 2 items (EMA)		X	X	X	X
Secondary outcomes						
Demographic variables (e.g., age, gender, pre-experience with chatbots)	Demographic Questionnaire		X			
Self-reported interoceptive accuracy	Interoceptive Accuracy Scale		X		X	X
Self-reported interoceptive accuracy	Awareness Scale of the Body Perception Questionnaire		X		X	X
Self-reported interoceptive accuracy	Interoceptive item (EMA)			X		
Body Awareness	Body awareness items (EMA)			X		
Mood	Visual Analogue Mood Scale (EMA)			X		
Mindfulness	Freiburg Mindfulness Inventory – short form (FMI)		X		X	X
General anxiety	General Anxiety Disorder (GAD-7)		X		X	X
Depression	Patient Health Questionnaire (PHQ-8)		X		X	X
Personality	Big Five Inventory (BFI-10)		X			
Emotion regulation	Emotion Regulation Questionnaire (ERQ)		X		X	X
Psychological well-being	WHO-5 Well-Being Index		X		X	X
Stress mindset	Stress Mindset Measure (SMM)		X		X	X
Intervention credibility and expectancies	Credibility / Expectancy Questionnaire (CEQ)		X			
Affinity for Technology	Affinity for Technology Interaction (ATI)		X			
Attitudes towards Artificial Intelligence	Attitudes towards Artificial Intelligence (ATAI) Scale		X		X	X
Satisfaction with the intervention	Client Satisfaction Questionnaire (CSQ-8)				X	
Usability of the app	Mental Health App Usability Questionnaire (MAUQ)				X	
Negative effects of the intervention	Inventory for the assessment of Negative Effects of Psychotherapy (INEP)				X	X
Adherence	Percentage of completed intervention units				X	
Dropout reasons	Dropout Questionnaire				X	
Open feedback questions regarding the chatbot					X	

Notes. EMA, ecological momentary assessment.

### Sample size estimation

2.9.

The sample size was calculated by an a-priori power analysis for a repeated measurement ANOVA *via* G*Power (126), comparing two groups. Assuming a small effect size of *f* = 0.15 (consistent with *d* = 0.30), based on an *α*-level of 0.05, a power of 0.90, and a dropout rate of 40%, the sample size analysis resulted in *N* = 130 participants (*n* = 65 in the intervention group, *n* = 65 in the control group). As previous findings regarding chatbot-based interventions in the area of mental health are sparse, the assumed effect size of *d* = 0.3 was determined based on a systematic review (127), reporting effect sizes of *d* = 0.29 for depression and *d *= 0.15 for anxiety. A review and meta-analysis based on online mindfulness-based interventions stated small effect sizes for mindfulness (*g* = 0.32), depression (*g* = 0.29), anxiety (*g* = 0.22), and well-being (*g* = 0.23). It needs to be noted that results regarding adherence, respectively, attrition rates in online or chatbot-based interventions are also sparse or often not reported (124, 55). The dropout rate of 40% is estimated based on the systematic review of adherence to web-based interventions (128) and the adherence rates of guided interventions (39, 45, 46).

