(1)the primary outcome perceived stress will be reduced in the intervention group compared to the treatment as usual control group.(2)the secondary outcomes interoception, mindfulness, and psychological well-being will be improved.Furthermore, we examine potential changes in secondary outcomes as health-related and related to the primary and main secondary outcomes, but not directly in the intervention targeted variables, e.g., depression, anxiety, emotion regulation, stress mindset and test for potential modifying effects on an exploratory level. For example, stress mindset could be a moderating factor of perceived stress (76, 77). Moreover, similar health-related measures had been investigated in the reported previous online or chatbot-based intervention studies (e.g., 55, 65–67). Additionally, based on previous research, we investigate user-oriented parameters such as usability, satisfaction with the intervention, and, lastly, adherence and potential dropout reasons, to potentially further improve the intervention for future research.

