#### Primary outcome: stress

2.8.1.

To screen the participants concerning their acute perceived stress levels as an inclusion criterion, the 10-item version Perceived Stress Scale (PSS-10; 92) is used. Acute perceived stress regarding the last month is rated as the degree to which situations in one's life are rated as stressful on a scale ranging from 0 = “never” to 4 = “very often”. Within the questionnaires from t1 to t3, the 4-item short scale (PSS-4) is implemented. The ratings on both scales are quantified as sum scores with higher scores representing higher perceived stress. The German version of the PSS-10 demonstrated good internal consistency (Cronbach's Alpha = .84; 93) and the PSS-4 exhibited acceptable and reliable psychometric properties across cultures (Cronbach's Alpha = 0.77, 94).

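### The sample size section claims 90% power at d = 0.30, but the conversion f = d/2 belongs to a between-group test that cannot give N = 130; for the interaction test that can, f = 0.15 is d of about 0.60 to 0.64

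*Protocol article*

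**What the plan says.** All of the following is in the protocol article.

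- Section 2.9 (Sample size estimation) describes an "a-priori power analysis for a repeated measurement ANOVA *via* G*Power (126), comparing two groups". The inputs are alpha 0.05, "a power of 0.90, and a dropout rate of 40" per cent, and an effect entered by "Assuming a small effect size of *f* = 0.15 (consistent with *d* = 0.30"). The result is N = 130, 65 per arm.
- The same section gives the origin of d: "the assumed effect size of *d* = 0.3 was determined based on a systematic review (127), reporting effect sizes of *d* = 0.29 for depression" and 0.15 for anxiety. It adds four pooled effects for online mindfulness programmes, from 0.22 to 0.32.
- The hypothesis at the end of section 1 (Background) is that "the primary outcome perceived stress will be reduced in the intervention group compared to the treatment as usual control group".
- Section 2.8.1 (Primary outcome: stress) fixes the waves: "Within the questionnaires from t1 to t3, the 4-item short scale (PSS-4) is implemented". The same scale is therefore measured three times.
- Section 2.10 (Data analysis) plans multilevel modelling of change over time by intention to treat, with imputation chosen according to the pattern of missing data.

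Section 2.9 does not say which F test was run, how many measurements were entered, or which correlation between them was assumed.

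**The concern.** In a repeated-measures ANOVA, f depends on the effect being tested. For the difference between two arms averaged over time, f = d/2, and this is the conversion behind the statement that 0.15 matches 0.30. For the group-by-time interaction, f measures how far the arm difference varies across waves, so the same d gives a much smaller f. If d/2 was entered into the interaction test, the N that comes out is too small for the d that went in.

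Section 2.9 is the article's only justification of N. If its equivalence fails, the trial is described as having 90% power for the small effect it is designed around, when it has that power only for a considerably larger one. The strength of evidence in a non-significant result depends on this.

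**Working it through.** **Inputs.** From section 2.9: f = 0.15, d = 0.30, alpha 0.05, power 0.90, dropout 40%, N = 130, two groups. From section 2.8.1: three PSS-4 waves (m = 3). Assumption: correlation ρ between waves, which is not stated; the range 0.5 to 0.7 is shown. Completers: 130 × 0.6 = 78. All powers use the noncentral F or t distribution.

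**1. The test for which f = d/2 is valid.** Between-group test: λ = N f² m / (1 + (m − 1)ρ), df = 1, N − 2. At f = 0.15 and m = 3, 90% power needs:

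- ρ = 0.5: 314 completers, 314/0.6 = 524 randomised.
- ρ = 0.6: 345 completers (346 for equal arms), 346/0.6 = 577 randomised.
- ρ = 0, the most favourable non-negative value: 158 completers. With 2 or 4 waves at ρ = 0 it is 236 or 120.

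All exceed 78, so N = 130 does not come from this test.

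**2. Reproducing 130.** Group-by-time interaction: λ = N f² m / (1 − ρ), df = (m − 1), (N − 2)(m − 1). With m = 3, ρ = 0.6 and N = 78, λ = 78 × 0.0225 × 3 / 0.4 = 13.16. Power is 90.6%, and 78/0.6 = 130 exactly. Other settings also give 78: m = 2 with ρ = 0.68, and m = 4 with ρ = 0.52. Inflating by 1.4 instead of dividing by 0.6 comes close with m = 3 and ρ = 0.52 (92 × 1.4 = 129). The main effect of time gives the same N numerically, but it does not test the treatment.

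**3. Converting d for the interaction.** If the arm difference at wave t is d_t with mean d̄, then f² is the average over waves of (d_t − d̄)²/4.

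- Differences (0, d, d): f² = (1/4)(1/3)(4/9 + 1/9 + 1/9)d² = d²/18, so f = d/4.24.
- Differences (0, d): f² = d²/16, so f = d/4. Four waves with (0, 0, d, d) also give d/4.

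Hence d = 0.30 is f = 0.071 (3 waves) or 0.075 (2 waves). Conversely, f = 0.15 is d = 0.15 × 4.24 = 0.64 or 0.15 × 4 = 0.60.

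**4. Interaction power at d = 0.30.** With m = 3, ρ = 0.6 and N = 78, λ = 78 × 0.005 × 3 / 0.4 = 2.925, which is 22% of the 13.16 above.

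| Setting | 78 completers | all 130 |
|---|---|---|
| 3 waves, ρ = 0.5 | 25% | 40% |
| 3 waves, ρ = 0.6 (gives 130) | 31% | 49% |
| 3 waves, ρ = 0.7 | 40% | 62% |
| 2 waves, ρ = 0.68 (gives 130) | 37% | 56% |
| 4 waves, ρ = 0.52 (gives 130) | 32% | 52% |

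**5. A more efficient analysis.** For the mean of t2 and t3 adjusted for t1, the residual variance in units of the outcome variance is (1 + ρ)/2 − ρ². For ρ = 0.5, 0.6 and 0.7 the SD is 0.707, 0.663 and 0.600. Power at d = 0.30 is 46, 51 and 59% with 39 per arm, and 67, 73 and 81% with 65 per arm. The d detectable with 90% power is roughly 3.24 × SD × √(2/n). It runs from 3.24 × 0.600 × √(2/65) = 0.34 to 3.24 × 0.707 × √(2/39) = 0.52 (0.53 with the t distribution).

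**6. What would rescue the claim.** With 78 completers, the 3-wave interaction reaches 90% at d = 0.30 only at ρ of about 0.91. That is not plausible for a four-item scale whose Cronbach's alpha section 2.8.1 gives as 0.77.

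**The case against.** The strongest reply is that the article does not disclose the settings, so no single power figure can be called the trial's own. This stands. Three waves with ρ = 0.6 is one of several settings that return 130. A reader might infer that power is 31% and the detectable effect 0.64 as facts; the documents do not support that, because both rest on inferred inputs. Leaving those settings to a fuller document is normal for an article and is not the fault raised here.

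Second, the sizing ANOVA on completers is not the planned analysis. Under the intention-to-treat multilevel model of section 2.10, participants with partial data would contribute, so 78 is a pessimistic count. This also stands, and it is why the baseline-adjusted figures, up to 81% with no loss, belong in the range. They remain below 90%.

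Third, a reader might add that the expected effect is itself below 0.30, since the six values in section 2.9 average 1.50/6 = 0.25. None of them is for perceived stress, and section 1 reports chatbot effects on psychological distress from d = 0.24 to 2.0. They do not establish the expected effect on the primary outcome.

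Fourth, a reader might conclude that a null result will be misread. The article does not say how a non-significant result will be interpreted, so this is a risk and not something the plan commits to.

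None of this restores the stated equivalence. Where f = 0.15 does match d = 0.30, N = 130 does not follow; where N = 130 follows, f = 0.15 does not match d = 0.30.

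**Conclusion.** Wrong as written. Section 2.9 joins an effect conversion from one test to a sample size that only a different test of the treatment effect reproduces. The claim of 90% power at d = 0.30 with 130 randomised and 40% dropout is not met in any plausible setting tried.

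At d = 0.30, power is about 25 to 59% with 78 completers and about 40 to 81% if all 130 contribute. The low ends are the 3-wave interaction and the high ends the baseline-adjusted mean, for correlations of 0.5 to 0.7. In the 2- and 3-wave interaction settings that return 130, it is about 31 to 37%. The d detectable with 90% power is about 0.60 to 0.64 in those settings, and about 0.34 to 0.53 under baseline adjustment, depending on dropout and correlation.

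These figures assume arms equal at t1, the same d at every later wave entered, and equal correlation between waves. If the effect were 0.30 at one of t2 and t3 and 0.15 at the other, the 3-wave interaction at ρ = 0.6 with 78 completers would have 24%. The failure of the equivalence does not depend on which inferred setting is true; the exact power does.

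**What to change.** Keep N = 130 and correct section 2.9:

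- Delete the parenthesis that equates f = 0.15 with d = 0.30.
- State the F test, number of waves and correlation actually entered in G*Power, and derive f for that test from d.
- From those settings, restate the d detectable with 90% power, and give power at d = 0.30 as a range under stated dropout and correlation, preferably for the planned multilevel model. The values above show what to expect; the sponsor should insert its own and not copy inferred ones.
- Add that a non-significant primary result will be interpreted from its confidence interval.

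The cost is rewording and a less favourable stated power. No extra participants are needed and the analysis is unchanged. Recomputing N for 90% power at d = 0.30 would be far more expensive: on the 3-wave interaction it needs 340 completers at ρ = 0.6, or 340/0.6 = 567 randomised (427 at ρ = 0.7, 707 at ρ = 0.5). That is not what is asked here.

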### Data analysis

2.10.

Multilevel modelling will be applied to analyse the longitudinal, nested data structure and change over time. The data analyses will be conducted according to the intention-to-treat principle. Procedures of imputation will be chosen based on patterns of missingness. The significance level for all analyses will be *p* ≤ 0.05. Exploratory mediation and moderator analyses including the primary and secondary outcomes and demographic variables will be conducted to examine how individual growth will be mediated or moderated by the according variables.

## Discussion

3.

The present study is designed to investigate the effects of a three-week chatbot-based intervention *via* smartphone, aiming to reduce stress and to improve various health-related parameters such as interoception in participants with medium to high stress levels. To the best of our knowledge, this is the first chatbot-based intervention addressing interoception, as well as in the context with the target variables stress and mindfulness. Strengths of the study are the design as a two-arm randomised controlled trial with a treatment as usual control group and outcome assessments pre-, post- and follow-up intervention as well as ecological momentary assessments, which is quite new in the assessment of interoception (90, 129, 130). Moreover, the highly standardized design is in line with the CONSORT guidelines (71, 73). In this context, the design of the present study and the usability of the chatbot was successfully tested in a previous feasibility study to establish a high quality, data security and usability of the intervention. Therefore, the user feedback had been implemented into the adapted version of the internally developed chatbot and will be analyzed to even potentially improve the intervention. Beyond that, the present study could shed light on the development of chatbots in the mental health area, in particular, for a stressed target group.

A possible limitation could be a limited attrition rate, as there is, for example, the issue of lacking long-term user engagement in e-Health (53, 131). One important factor in this context might be the feeling not to interact with a “real” human (132). At the same time, it needs to be highlighted that adherence rates of online or chatbot-based interventions are often not reported or were operationalised by diverse assessments (55, 124). To counteract a low adherence of the chatbot-based intervention, we implemented high guidance by the chatbot, short sessions, individual and flexible time points of the intervention units and the ecological momentary assessments, reminder SMS, and the opportunity to postpone single units. At the same time, the intervention is supposed to be used in everyday life, i.e., it should be provided in real time, in a natural setting, diverse contexts, comparably to ecological momentary interventions (133, 134). Additionally, the intervention contains personalised elements which are considered to be essential for chatbots in the area of health care, e.g., for user satisfaction and user engagement (135). Moreover, 53 concluded the significance of usability and interactivity in the context of mental health technology. Further limitations of the study might consist in the risks of measurement reactivity, especially in the context of digital ecological momentary assessments (136), or the systematic self-report bias in health data (137) due to self-report measures only. Moreover, as reported in the study by (138), differences to physiological assessments are possible, which are not part of the current study. To address the challenges of a potential gender bias and self-selection by participants with a high technical or online affinity, the chatbot was named gender-neutral, no avatar image of the chatbot is presented, and broad, nationwide recruitment strategies are realized (e.g., 65).

## Ethics and dissemination

The trial has been approved by the ethics committee of Ulm University (No. 401/20) and registered in the German Clinical Trials Register (DRKS00027560) on 06 January 2022. Participants in the study will receive written information on study conditions, data security, voluntary participation, the right to leave the study at any time, and the publication of anonymised results. Written informed consent will be obtained from all participants prior to their participation. In the present study, only self-report data but no psychophysiological data will be assessed. Data collection by the chatbot will happen on a secure on-premises server with limited access by a single team member. Online questionnaires *via* Unipark will be pseudonymised and linked to the conversations with a random token. All personal information as well as the tokens’ coding list will only be stored on the secure server and will be deleted after the study is completed. Only pseudonymised data is stored on a secured cloud storage with restricted access to the remaining authorised study personnel obliged to secrecy. According to German law, data will only be shared with parties outside the project team in anonymized form. Trial results will be submitted for publication in a peer-reviewed journal and presented at conferences.
